### Concomitant treatment

Participants are able to continue routine medications such as nonsteroidal anti-inflammatory drugs, acetaminophen, analgesics and antidepressants, and maintain their usual treatment visits with their primary care physician or rheumatologist throughout the study. Participants are not required to wash out their pain medications prior to the start of the study. The research staff records any changes made to treatment but do not change or recommend changes in medical therapy.

### Measurements

Fibromyalgia outcome measurements are drawn from the key variables recommended by the new 2010 American College of Rheumatology Criteria [36] and focus on fibromyalgia symptom severity and body pain. We assess physical, psychological, and psychosocial variables for fibromyalgia that are well-documented in clinical care and research [11]. Every participant is evaluated at baseline (prior to starting either intervention), after completing the intervention (12 or 24 weeks later), and at 24-week and 52-week follow-ups (Table 1). Durability assessments up to 52 weeks are informative for clinical practice based on prior data.

### Primary outcome

The primary outcome measure is change in the FIQR score between baseline and 24 weeks. The FIQR is a well-validated multidimensional instrument that measures participant-rated overall severity of fibromyalgia, including intensity of pain, physical function, fatigue, morning tiredness, depression, anxiety, job difficulty, and overall well-being [35]. Each item is standardized on a scale ranging from 0 to 10, with lower scores indicating more improvement or less negative impact. In addition, FIQR is also assessed weekly during the intervention period for all groups of participants as well as at the 52-week time points as secondary outcomes.

### Secondary outcomes

It is essential in fibromyalgia treatment studies to measure a wide spectrum of variables due to the complex nature of fibromyalgia and the importance of seeking subsets of responses in this study.

#### Psychological and psychosocial functioning measures

The Patient’s Global Assessment (Global Visual Analogue Scale) is a visual analogue scale that measures the level of fibromyalgia severity on a 10-point scale with 10 reflecting the most extreme severity and 0 reflecting no severity.

Health Related Quality of Life assessments are made using the Medical Outcome Study Short Form 36 Health Survey (SF-36) [43]. The SF-36 is a self-administered, 36-item questionnaire that assesses the concepts of physical functioning, role limitations due to physical problems, social function, bodily pain, general mental health, role limitations due to emotional problems, vitality, and general health perceptions. Summary scores include physical function, mental function, and combined total function. Scores range from 0 to 100, with higher scores indicating better health status [44].

The Beck II Depression Inventory (BDI) is a 21-question, validated, self-report instrument that measures the severity of depressive symptoms. Higher scores reflect a greater degree of symptom severity [45].

The Pittsburgh Sleep Quality Index is an 11-item, validated, self-report questionnaire that measures sleep quality. Lower scores are associated with better sleep quality [46].

The Coping Strategies Questionnaire is a seven-item, validated, self-report questionnaire assessing pain coping, consisting of six cognitive and one behavioral scale. Higher scores reflect greater usage of coping strategies [47].

The Hospital Anxiety and Depression Scale is a 14-item, validated, self-report questionnaire that assesses levels of depression and anxiety. Higher scores reflect greater levels of anxiety and depression [48].

The Perceived Stress Scale is the most widely used psychological instrument for measuring the perception of stress. The 10-item scale also includes a number of direct queries about current levels of experienced stress. For this instrument, higher scores reflect a greater degree of symptom severity [49].

The Chronic Pain Self-Efficacy Scale is a modified version of The Arthritis Self-Efficacy Scale that has been validated for patients with chronic pain [50]. It contains eight questions divided into three subscales (pain coping, physical functioning, and coping with symptoms). The score is obtained by means of a Likert scale with a range of 0 to 10, where higher scores indicate better self-efficacy.

The Medical Outcome Study Social Support Survey assesses social support by using the Social Support for Physical Activity Scale adapted from Cohen and colleagues [51]. It comprises 19 questions rated from 0 to 5 to assess the influences that family and friends have on patients as they perform regular physical activity. Higher scores reflect more perceived social support from these individuals.

Outcome expectations are beliefs that carrying out a specific behavior such as physical activity will lead to a desired outcome. The brief, validated, outcome expectations scale [52] contains nine questions that ask about physical and mental benefits and are used to assess outcome expectations. Scores can range from 1 to 5, with 1 indicating low outcome expectations for the exercise and 5 suggesting high outcome expectations. This questionnaire is used prior to randomization to assess the outcome expectation for any exercise intervention. It is also assessed after randomization prior to the first session to assess the outcome expectation for the assigned intervention.

Participants enrolled in the trial also complete seven Participant-Reported Outcomes Measurement Information System (PROMIS) static short-forms, version 1.0 instruments, including PROMIS Pain Impact (six items), Physical Functioning (10 items), Emotional Distress-Anxiety (seven items), Emotional Distress-Depression (eight items), Sleep Disturbance (eight items), Health Assessment Questionnaire (twenty-seven items) and Satisfaction with Participation in Social Roles (seven items) [53].

The Health Assessment Questionnaire, developed originally at Stanford in the late 1970s to assess patients with rheumatoid arthritis, has been validated in a broad range of rheumatic and non-rheumatic disease populations [53-57]. It is a 20-item, self-report questionnaire which measures functional status (disability). Higher scores indicate greater disability.

The NEO Five-Factor Inventory is a validated 60-item questionnaire that measures the five domains of personality including neuroticism, agreeableness, conscientiousness, extraversion, and openness [58]. It consists of five 12-item, five-point Likert scales that measure each of the domains. Higher subscores indicate higher levels of each personality trait.

The Five Facet Mindfulness Questionnaire is a validated, 39-item questionnaire that measures five facets of mindfulness: observe, describe, act aware, nonjudge, and nonreact [59]. Participants answer each of the questions on a five-point Likert scale with higher scores reflecting higher mindfulness.

The Credibility/Expectancy Questionnaire is a validated, six-item instrument that assesses how believable, convincing, and logical the treatment seems to the participant as well as what improvements the participant thinks will be achieved. This questionnaire has been adapted to reflect the participant population of this study. Higher scores reflect greater credibility and expectancy by the participant [60].

The Pre-Clinical Disability Questionnaire is an adapted 12-item, yes/no questionnaire that assesses whether participants have changed the way or how often they do a series of daily activities such as climb a flight of stairs or carry groceries [61]. More positive answers reflect greater preclinical disability.

The Community Health Activities Model Program for Seniors is as Physical Activity Questionnaire for Older Adults and a validated, 40-item questionnaire that measures weekly physical activity levels for older adults by calculating caloric expenditure [62] and frequency of various common exercises completed by older adults such as swimming or walking. Higher scores reflect greater physical activity levels.

#### Physical function performance

Physical function assessments include the timed chair stand, the 6-minute walk test, functional balance, and lower extremity strength and power.

The timed chair stand tests measures time taken to complete ten full stands from a sitting position and is a reliable measure of lower body strength and dynamic balance [63,64]. The recorded time is the average on two attempts.

The 6-minute walk test is a reliable measure of functional exercise capacity [65,66]. Participants are asked to walk as fast and as far as possible within the 6-minute period. Participants are given verbal encouragement every minute throughout the 6 minutes and are informed of the remaining time every minute. The distance in meters covered at the end is noted and recorded.

One leg stand is defined as standing on one foot without shoes with the contralateral knee bent and not touching the weight bearing leg; the hips are level to the ground. The test is conducted on the dominant and nondominant leg with the eyes open and closed (four conditions). We defined the dominant leg as the leg that the participant said they would use to kick a ball.

The evaluator used a standardized script throughout the assessment. If the participant is not comfortable performing the single-leg stand test for any condition (for example, eyes closed non-dominant leg) then they can skip that part of the test. If the participant is comfortable then they will first balance with their eyes open on their dominant leg for 30 seconds or until the participant uses their arms or opposite leg for support (for example, bracing the nonweight-bearing leg against the weight-bearing leg), or hops on the weight-bearing leg. The participant will have up to five trials to reach 30 seconds. Participants will take a 30-second break between trials [67-70]. After completing the trials with eyes open and on the dominant leg the participant will repeat these steps for the three remaining conditions in a standard order: 1) eyes open, nondominant leg; 2) eyes closed, dominant leg; and 3) eyes closed nondominant leg.

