**Methods/design:**

A single-center, 52-week, randomized controlled trial of Tai Chi versus aerobic exercise is being conducted at an urban tertiary medical center in Boston, Massachusetts. We plan to recruit 216 patients with fibromyalgia. The study population consists of adults ≥21 years of age with fibromyalgia who meet American College of Rheumatology 1990 and 2010 diagnostic criteria. Participants are randomized to one of four Tai Chi intervention groups: 12 or 24 weeks of supervised Tai Chi held once or twice per week, or a supervised aerobic exercise control held twice per week for 24 weeks. The primary outcome is the change in Revised Fibromyalgia Impact Questionnaire total score from baseline to 24 weeks. Secondary outcomes include measures of widespread pain, symptom severity, functional performance, balance, muscle strength and power, psychological functioning, sleep quality, self-efficacy, durability effects, and health-related quality of life at 12, 24, and 52 week follow-up.

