Secondary analyses will examine change in FIQR from baseline to 12 and 52 weeks as well as secondary outcomes for change at 12, 24, and 52 weeks. Continuous outcomes will be compared by linear regression, and discrete outcomes by logistic regression. All analyses will follow the template for the primary outcome in the previous paragraph, using mixed models with adjustment for instructor examining treatment duration and frequency. If the instructor effect is not significant, we will present results summarized across instructors. All regression models will be assessed by regression diagnostics for adherence to model assumptions. To explore potential psychological and psychosocial mediators (for example, depression, self-efficacy, social support) that may be useful in future research, we will examine treatment interactions with a list of pre-defined moderators. To control for multiple testing, we will perform these tests at a conservative significance level adjusted for the number of moderators tested. In addition, we will also perform longitudinal analyses in which measurements at baseline, 12, 24, and 52 weeks are jointly analyzed using appropriate mixed models including time as a categorical fixed factor with random intercepts and first-order autocorrelation of the errors. Similar mixed models will be used to examine the weekly FIQR measurements taken in the intervention period. We will also check for potential confounding and interaction between time, treatment, instructor and other significant covariates. In addition to intent-to-treat analyses in which dropouts are treated as having no effect, we will also perform secondary analyses using multiple imputation and checks of the mechanism by which participants drop out to determine whether ignorable or nonignorable missing data methods are required [74,75]. If nonignorable methods are needed, we will explore both selection and pattern-mixture types [74,75].

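### The one-leg stand stops at 30 seconds, so a participant already at 30 s at baseline cannot show a gain, and the planned linear analysis of change suits such a capped outcome badly.

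*Protocol article*

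**What the plan says.** The Methods/design part of the abstract lists "functional performance, balance, muscle strength and power" among the secondary outcomes. The section Physical function performance describes the one-leg stand: dominant and nondominant leg, each with eyes open and closed. In a trial the participant balances "for 30 seconds or until the participant uses their arms or opposite leg for support", or hops. On attempts it says: "The participant will have up to five trials to reach 30 seconds". A participant who is not comfortable with a condition is told of a way out: "then they can skip that part of the test".

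The Data analysis section sets out secondary analyses of FIQR change "as well as secondary outcomes for change at 12, 24, and 52 weeks". The model is then named: "Continuous outcomes will be compared by linear regression, and discrete outcomes by logistic regression". These analyses follow the template of the primary outcome, that is, mixed models with instructor as a blocking factor. Under that template, baseline characteristics enter only if they differ substantially between groups. All regression models are to be checked by diagnostics. No method for an outcome with an upper limit is named.

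**The concern.** The article fixes three things that fit badly together: a hard stop at 30 s, repeated attempts that help participants reach it, and a linear comparison of raw change. Whoever holds 30 s at baseline in a condition can stay level or get worse, but cannot gain. If many are there, the observed between-group difference in change shrinks for reasons of the instrument, and the raw change score adds noise that a baseline-adjusted analysis would remove.

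The endpoint is not incidental to the intervention. The Tai Chi intervention section says that the ten forms were chosen partly because they load postural stability progressively, moving from support on both legs to support on one. A difference lost to the cap could be read as an absence of benefit on the skill that these forms train.

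**Working it through.** **1. The plan's own power figure.** It concerns the FIQR: 144 v 72, standardised effect 0.4, two-sided 0.05. √(144 × 72 / 216) = √48 = 6.93; 0.4 × 6.93 = 2.77; 2.77 − 1.96 = 0.81; Φ(0.81) = 0.79. This reproduces the stated value of about 80%. No figure is stated for the one-leg stand.

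**2. What the cap does to the estimate.** Illustration with a normal latent hold time, visit correlation 0.5 or 0.7, effect of 0.4 SD of change, 144 v 72, and a t-test on observed change (3,000 runs per scenario; values approximate, averaged over the two correlations):

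| Share at 30 s at baseline (assumed) | Estimate / latent effect | Power |
|---|---|---|
| 0% | 1.00 | 0.79 |
| 10% | 0.87 | 0.75 |
| 20% | 0.74 | 0.68 |
| 30% | 0.64 | 0.65 |
| 50% | 0.43 | 0.50 |
| 70% | 0.24 | 0.34 |

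With no true effect (correlation 0.7; cap shares of 0, 30 and 50%), the rejection rate was 0.049 to 0.051, so type I error is not inflated.

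**3. What five attempts do.** If the best trial is scored (an assumption; the article does not say), the chance of a capped score is 1 − (1 − p)^5. For p = 0.10, 0.20 and 0.30 per trial, and independent trials, this is 0.41, 0.67 and 0.83.

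**4. Comparing analyses of the same capped data.** Assumptions: log-normal times with log SD 1, visit correlation 0.7, latent effect 0.4 SD, 144 v 72. The effect equals 0.4 / √(2 × (1 − 0.7)) = 0.4 / 0.775 = 0.52 SD of change, larger than the 0.4 used for the FIQR, so levels in steps 2 and 4 are not interchangeable.

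| Share at 30 s at baseline (assumed) | Linear change, seconds | Follow-up adjusted for baseline | Censored model with baseline covariates |
|---|---|---|---|
| 20% | 87% | 92% | 96% |
| 40% | 78% | 88% | 94% |
| 60% | 63% | 77% | 81% |
| 80% | 36% | 54% | 58% |

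Baseline adjustment adds 5, 10, 14 and 18 points; the censored model adds a further 4, 6, 4 and 4. Except at 20%, where the two steps are about equal, most of the gain is baseline adjustment.

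**5. What adjustment does and does not repair.** Randomisation makes the expected baselines equal, so the difference in mean change equals the difference in mean follow-up in expectation: (E[Y₁] − E[B]) − (E[Y₀] − E[B]) = E[Y₁] − E[Y₀]. Change and baseline-adjusted follow-up therefore target the same capped difference. Adjustment buys precision; it does not undo the shrinkage in step 2. Only an analysis that treats 30 s as censored addresses that, under its own distributional assumptions.

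**The case against.** Several points on the other side stand. The planned models are mixed models adjusted for instructor and checked by diagnostics, and a joint longitudinal analysis of all visits is added. Diagnostics could reveal bunching at 30 s. But none of these removes a ceiling, and no alternative is named in advance. The cap works condition by condition, so a ceiling with eyes open need not reach the eyes-closed conditions. The timed chair stand is also described as reflecting dynamic balance. The one-leg stand is one component of one row in a long list of secondary outcomes in Table 1.

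The size must not be overstated. A reader might set the capped powers in seconds against an uncapped figure of about 95%. That figure is on the log scale. Uncapped change in seconds has only about 71% power under the same assumptions, because of the long right tail, so a cap reaching 20% or 40% does not lower power on that scale. The fair comparison is between analyses of the same capped data, as in step 4 of the working.

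A reader might also infer from the skip rule that the worst balancers leave the balance endpoint. The document does not support this. The ground for skipping is discomfort, it applies to one condition at a time, and nothing says that skipped conditions are excluded; scoring as zero or imputation would be equally compatible with the text. Scoring of skips and trials is detail that an article may leave to the full protocol or SAP.

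**Conclusion.** The point holds for the ceiling. The 30 s stop with up to five trials, combined with a linear analysis of raw change, pulls the estimated balance difference towards zero in any condition where participants start at the limit, and uses the data less efficiently than a baseline-adjusted analysis. Under the stated assumptions the avoidable loss of power against baseline adjustment runs from about 5 points with 20% at the cap to about 18 points with 80%.

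The size in this trial is unknown, because the document gives no distribution of hold times. That eyes-open conditions are most exposed is an expectation, not a documented fact. The harm is attenuation and lost power on one secondary test. Type I error stays at about 5% in the scenarios run, and the FIQR analysis and sample size are untouched. No conclusion about bias from skipped conditions can be drawn from the article.

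**What to change.** In the Data analysis section, for the one-leg stand:

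- Analyse follow-up time separately for each condition, within the planned instructor-adjusted mixed model, with baseline time and an indicator for 30 s at baseline as covariates whether or not the groups differ at baseline.
- Add a sensitivity analysis that treats 30 s as right-censored, or that uses an ordinal outcome.
- Report by arm and visit the share at 30 s and the share who skipped each condition.
- State in the SAP how a skipped condition is scored.

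The cost is analysis wording; no new measurement is needed. The downside is that a censored or ordinal effect is less direct to interpret than a difference in mean seconds, which is why it is proposed as a sensitivity analysis. The baseline-adjusted analysis still estimates a capped difference, so the share at 30 s should be read beside it.

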#### Measures of muscle strength/power

Participants’ muscle strength and power is measured using a leg press. Participants are seated on the bilateral leg press apparatus with knees flexed to 90 degrees and hips flexed to approximately 110 degrees (Leg Press A420, Keiser Corporation, Fresno, CA, USA). Knee angle is measured using an electrogoniometer (AD Instruments, Colorado Springs, CO, USA). Each participant is given the opportunity to familiarize themselves with the testing equipment through the use of a visual demonstration and practice at low resistances. Force, position, and velocity of each repetition are sampled at 400 Hz and saved to disk for offline analysis. Using software provided by the manufacturer, these data are then converted to force, position and velocity at the footplate (Software Release 7.8, Keiser Corporation). Leg extensor muscle strength are quantitatively assessed using the one-repetition maximum (1RM) technique and are defined as the maximum load that could be moved only once throughout the full range of motion (ROM) while maintaining proper form [71]. Subjects perform the concentric phase, maintain full extension, and perform the eccentric phase of each repetition over 2, 1, and 2 seconds, respectively. After measurement of the 1RM, assessment of leg press peak muscle power is made after a 5-minute rest period. Performance of this multiple attempt peak power test has been previously described and validated [71]. Briefly, each participant is instructed to complete a total of five repetitions each separated by 30 seconds as quickly as possible through their full ROM at both 70% and 40% of the 1RM. The highest measured power output is recorded as the leg press peak power.

#### Accelerometry

Accelerometry allows objective measurement of physical activity by the use of a motion sensor which records both the number and magnitude of vertical accelerations generated by human movement. This allows both volume and intensity of activity to be registered. In this study, accelerometry measurements are performed using the Actigraph Model 7164 (Manufacturing Technology Inc., Pensacola, , FL, USA). The actigraph is worn superior to the iliac crest in a custom pouch, secured to the participant’s belt by a Velcro fastener. Participants are instructed to wear the actigraph during the baseline and follow-up visits for a consecutive 7-day period, excluding sleep and bathing time. Activity is recorded using 1-minute epochs and participants also complete a log to record when the actigraph was worn.

### Adherence

Our trained staff remind participants of home practice, monitor adverse events, and ensure completion of exercise logs/diaries. All participants are encouraged to maintain their usual physical activities, but to perform no new formalized exercise program. We track the number of missed sessions for each participant during the intervention period. Participants’ attendance is monitored during each in-person session (12 or 24 for Tai Chi and 24 weeks for aerobic exercise) by staff-completed attendance forms as well as class sign-in sheets for the Tai Chi intervention. Participants are also asked to maintain daily Tai Chi or aerobic exercise practice throughout the follow-up period and are encouraged with phone calls from the research staff once a month until the end of the 52 weeks using standardized questionnaires. Adherence is measured post-intervention by these calls during which research staff ask about the frequency and duration of the Tai Chi and aerobic exercise. as well as which exercises were done by those participants in the aerobic exercise intervention.

